### Selection/Treatment of Subjects

The first 200 TIP-OA clients who provide informed consent will participate in data collection for research.

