##### Additional measures/covariates

*Baseline risk:* during the screening process, our clinician team codes clients as green (low risk), orange (medium risk), or red (high risk) (Appendix B in Supplementary Material), chiefly in order to match clients with appropriately skilled and experienced volunteers. Demographics: Age, living situation, education, mental illness diagnoses, and psychotropic medication use will be obtained at baseline. *Digital Literacy:* We will systematically measure digital literacy using the Technology in Geriatric Psychiatry scale, which is a 14-item questionnaire about patients' access to technological devices, comfort or familiarity with software, availability of family members who can assist in setting up technology, interest in learning to use video conferencing software, and interest in receiving support via videoconferencing. This scale was developed by co-investigator [name] from Harvard University and is currently being validated in another study.

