### Data Analysis

#### Quantitative Analysis

Descriptive statistics for continuous variables will include means and standard deviations, while categorical variables will be summarized using frequencies and proportions. A within-subjects repeated measure analysis of variance (ANOVA) will be conducted for the PSS (primary outcome), COVID Fear Scale, PHQ-9, GAD-7, and mental healthcare utilization (secondary outcomes) to assess differences in measures between baseline and the 8-week follow-up between groups with different baseline risk (low, medium, and high risk). Additional analysis of covariance (ANCOVAs) will control for variables that differ between groups at baseline. We will use LOCF to handle missing data that results from study attrition. Although we have found it extremely rare to be missing baseline data when, for example, a participant answers all but one question on a measure, in any such case we will exclude the participant's data for that measure. All ANOVAS will be tested at two-tailed alpha = 0.05. Linear mixed effect regression models, adjusting for age and sex, will analyze the effect of TIP-OA on all outcomes (PSS, COVID Fear Scale, PHQ-9, GAD-7, and mental healthcare utilization) collected at baseline and 8-week follow-up. We will perform additional linear mixed effect regression models accounting for a larger group of important variables such as client referral source (e.g., referred from clinic vs. self-referred) and cognitive functioning (e.g., suspected mild dementia vs. no suspected mild dementia) on mental health outcomes. Variable selection in linear mixed effect model (32) will be used to select important fixed effect covariates as they relate to the outcome. The fixed effect point estimates and corresponding confidence intervals and *p*-values will be computed. Additional subgroup analyses will also compare the primary outcome (PSS) between important subgroups [e.g., referral source (referred from clinic vs. self-referred) and cognitive functioning (suspected mild dementia vs. no suspected mild dementia)]. Analyses will be run using R statistical software.

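### In the additional mixed models, covariates are selected on the outcome and then tested on the same 200 clients, with no stated allowance for the selection

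*Protocol article*

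**What the plan says.** The Quantitative Analysis section of the protocol article has two tiers of mixed model.

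- **Main tier.** The adjustment set is fixed: "Linear mixed effect regression models, adjusting for age and sex, will analyze the effect of TIP-OA on all outcomes".
- **Additional tier.** The candidate list is open: "We will perform additional linear mixed effect regression models accounting for a larger group of important variables such as client referral source", with suspected mild dementia as the other example. The section then states "Variable selection in linear mixed effect model (32) will be used to select important fixed effect covariates as they relate to the outcome". The method is given only by that citation.

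The next sentence reads "The fixed effect point estimates and corresponding confidence intervals and *p*-values will be computed". No hold-out sample, resampling, selection-adjusted inference or exploratory label is stated for these results. The data come from one cohort: "The first 200 TIP-OA clients who provide informed consent will participate in data collection for research".

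**The concern.** A covariate that enters a model because it is associated with the outcome in these data has already passed a test on these data. If the interval and p-value are then computed as though the model had been fixed in advance, they ignore that step. Among covariates with no true effect, the survivors are the ones that looked associated by chance, so their error rate is no longer 5% and their coverage no longer 95%.

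What is at stake is any statement about which kinds of client have better or worse mental health scores. The study has one group and no control, so contrasts between kinds of client are among its few comparative results. Referral source and suspected mild dementia are the two factors the article names for these models.

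**Working it through.** The plan gives no error rate or coverage for these models, so there is no figure to reproduce. The check is an illustration under stated assumptions.

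**Inputs from the article**
- 200 clients, one cohort (Selection/Treatment of Subjects).
- Two analysed time points, baseline and 8 weeks (Quantitative Analysis).
- Two-sided 0.05. The article states this for the ANOVAs ("All ANOVAS will be tested at two-tailed alpha = 0.05"); it is assumed for the mixed models.
- About 8 candidates. Four come from the demographics list ("Age, living situation, education, mental illness diagnoses, and psychotropic medication use will be obtained at baseline"), leaving out age: living situation, education, diagnoses and psychotropic use. The other four are baseline risk, digital literacy, referral source and cognitive status. The range 6 to 10 was used.

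**Assumed**
- Random-intercept model, within-client correlation 0.6, independent time-invariant covariates, total residual SD 1.
- Backward elimination, keeping a term at p≤0.157 (AIC-like) or p≤0.05.
- 4,000 runs per scenario.

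**Hand check for a null covariate.** Its p-value is uniform, so with one candidate P(p<0.05 | kept) = 0.05/0.157 = 32%. The 95% interval misses zero exactly when p<0.05, so coverage among kept terms is 1 − 0.32 = 68%. Under a p≤0.05 rule, every kept null term is significant and coverage is 0% by construction.

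**Simulation, all candidates null, AIC-like rule**

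| Candidates | Kept null terms with p<0.05 | Coverage of kept null terms |
|---|---|---|
| 6 | 32.0% | 68.0% |
| 8 | 32.7% | 67.3% |
| 10 | 34.8% | 65.2% |

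**Simulation, one real effect among 8 candidates, when that covariate is selected**

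| True effect (per SD of covariate) | Mean estimate, AIC-like | Mean estimate, p≤0.05 | Overstatement |
|---|---|---|---|
| 0.10 | 0.144 | 0.166 | 44–66% |
| 0.15 | 0.171 | 0.186 | 14–24% |
| 0.20 | 0.204 | 0.215 | 2–7% |

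Coverage for these real effects stayed between 93% and 98%. The coverage failure is therefore confined to covariates with no effect; for weak real effects the fault is overstatement.

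**Chance of at least one false-positive covariate per outcome**

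| Null candidates | No selection, 1 − 0.95^k | AIC-like | p≤0.05 rule |
|---|---|---|---|
| 6 | 26% | 27% | 25% |
| 8 | 34% | 35% | 33% |
| 10 | 40% | 44% | 41% |

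For 12 candidates, 1 − 0.95^12 = 46%. Selection adds at most about 4 points here.

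**Pre-post change.** With both visits present and time-invariant covariates, the average change is orthogonal to the covariates. It reduces to a paired comparison, whatever is selected. Its type I error was 4.8–5.6% in every scenario.

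**The case against.** **The method is not visible.** The selection procedure is given only by citation, and the article says just that the quantities will be computed; that they are unadjusted is an inference from its silence. This stands as a limit on size and direction. A reader might infer that the estimates are necessarily biased away from zero, but a penalised method could shrink them. Intervals and p-values with no allowance for the search would still be invalid.

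**An article leaves such detail to the SAP.** This stands for the candidate list and the selection rule. It does not answer the point, because the article affirmatively commits to outcome-driven selection followed by inference. An analysis plan that carried this out as written would carry the fault with it.

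**False-positive rates may look like proof.** A simpler simulation, with one outcome value per client and backward AIC, gave a 36%, 43% and 48% chance per outcome of at least one significant noise covariate among 8, 10 and 12 candidates. A reader might take this as the damage done by selection. It is not: without selection the figures are 34%, 40% and 46%. This is ordinary multiplicity, and a pre-specified full model would not remove it.

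**The main results may seem at risk.** The documents do not support that reading. The age- and sex-adjusted models and the ANOVAs use no selection step, nor do the separate subgroup comparisons of PSS. Finding predictors is also not one of the article's listed objectives, which limits the weight of the point.

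**Covariate sets may differ by outcome.** They could, since the search is run outcome by outcome, but that is not an error in itself.

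**Conclusion.** The concern holds for the additional, covariate-selected mixed models only. Unless the cited method corrects for selection, the intervals and p-values of selected covariates are too optimistic. The size depends on the assumed rule, on 6 to 10 independent candidates and on a within-client correlation of 0.6. The loss of coverage to about two thirds applies to selected covariates with no effect. Overstatement is large for weak real effects and small by 0.20 SD. The direction of bias in the estimates is not settled while the cited method is unseen. This is a minor to moderate fault in statements about covariates and is worth correcting, but it does not threaten the PSS result.

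**What to change.** Replace outcome-driven selection in the additional models with one covariate set fixed in advance from variables already collected or named in the plan: age, sex, baseline risk, referral source, suspected mild dementia, living situation, education, mental illness diagnosis, psychotropic use and, if wanted, digital literacy. Code it sparingly for 200 clients. With three risk levels (2 terms) and one term for each of the other eight variables, this is 10 terms, or 11 with digital literacy, which leaves 200/10 = 20 or 200/11 ≈ 18 clients per term. Fit the full model once per outcome, take the intervals from it, and read covariate p-values with multiplicity in mind, since pre-specification does not remove that.

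If selection is kept, label those results exploratory and report bootstrap selection frequencies instead of p-values.

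Only the analysis wording changes. The cost is a few degrees of freedom spent on weak covariates.

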#### Qualitative Analysis

A descriptive phenomenological approach will be used to analyze qualitative data. This descriptive thematic analysis will focus on the lived experiences of clients, volunteers, and stakeholders in order to map out the broader phenomena emerging from TIP-OA. We will code data based on repeated patterns of words, key-words-in-context (KWIC), contrasting information, and by searching for missing data. These patterns will help to identify and organize themes based on frequency, recurrence, and complexity of meanings in the data. Using a gender lens, participant narratives will be analyzed to understand their experiences. Coding will take place in three phases. Phase 1 will be descriptive, classifying the participants' narratives into standardized, predefined codes. In phase 2, descriptive coding will inform categorical coding by helping to further define data categories. In phase 3, analytical coding will allow interpretation of data-grounded emergent themes. To establish and authenticate links between different sources, we will conduct data triangulation by approaching individual narratives from various sources. We will use NVIVO (33) to establish frequencies of codes within narrations along with the source, quality, and depth of the content.

### Sample Size Justification

Comparable intervention studies for late-life stress, fear, depression, and anxiety have detected statistical significances and clinically meaningful effects (20, 34) including one volunteer-based program with a sample size of 150–200, which showed efficacy in preventing episodes of major depression in older persons with subsyndromal symptoms (19).

## Results—Early Experience

As of October 15th, 2020, 150 volunteers have been trained to provide TIP-OA to 305 older clients. Final research ethics approval has been provided and we will consecutively recruit 200 clients for quantitative data collection. After 8-weeks, 16 volunteers and eight clinicians will be consecutively selected for Zoom^TM^ focus groups, and 25 clients, 15 volunteers, and 10 stakeholders will be selected in the same manner for semi-structured interviews on Zoom^TM^.

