Currently, global healthcare systems are overburdened, with professionals increasingly becoming burnt out, reassigned, or infected (17, 18). Additionally, most experts agree that a second wave of infection will occur in the fall of 2020 (19), thus implementing community-based volunteer interventions could aid current mental health support services by preventing the development or worsening of mental health issues. For example, in India, a successful mental health intervention with lay volunteers improved depression and other psychiatric symptoms in older adults by providing problem-solving strategies, health education, and assistance in accessing medical and social programs (20). Indeed, not all telehealth modalities may be accessible to older adults (21); one survey found that only 10% used the internet, while 72% owned a cell phone (22). In the context of COVID-19, many telehealth interventions requiring advanced digital literacy are likely unfeasible for rapid implementation due to a lack of infrastructure, training, and low rates of digital literacy in older adults (23). Given these limitations, telephone-based care is likely able to serve the largest proportion of older adults. Thus, we have started a novel volunteer-based telehealth intervention program for older adults (TIP-OA) in Montreal, Canada. The objective of the study is to assess the efficacy of this program by:

Evaluating the effects on perceived stress, fear related to COVID-19, symptoms of depression and anxiety in older adults (i.e., clients), as well as the effects on mental healthcare utilization.Comparing clients' mental health outcomes based on baseline risk (i.e., low, medium, or high risk).Analyzing the experiences of clients, clinicians, volunteers, and organizers/stakeholders involved in the program using semi-structured interviews and focus groups.

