#### Telehealth Intervention Program for Older Adults (TIP-OA)

#### Recruitment and Training of Volunteers

Volunteers are recruited (1) using an advertisement circulated on social media; (2) through direct recruitment of medical, social work, psychology, and nursing students from McGill University; (3) from the research and clinical teams' social networks; and (4) through the Jewish General Hospital (JGH) Foundation and Auxiliary, a volunteer non-profit organization. Interested individuals are rigorously screened and interviewed using Zoom^TM^, a widely used video conferencing platform. Selected inclusion criteria are the ability to (1) commit for a minimum of 3-months; (2) provide this service to 3-5 clients; and (3) call each client at least once every week. Applicants with a criminal record or applicants who refuse to submit to a background check are excluded from volunteering.

Members of the volunteer management team stratify volunteers according to past volunteering and clinical experience(s) (Appendix A in Supplementary Material). Two trainers facilitate two weekly 2-h training sessions over Zoom^TM^, to a maximum of five volunteers per session (please contact [contact] for more information regarding the training design and/or manual). The initial virtual training was provided in kind collaboration with the Touch-Volunteers in Partnership (ViP) program at the Jewish General Hospital. The Touch ViP program was created through a participatory mixed-methods study, which engaged persons living with mental health conditions, their families, and mental health professionals over 3 years to support recovery-oriented practices (24, 25). The Touch Volunteer Manual, originally designed for in-patient services, was adapted for telehealth and is provided to TIP-OA through the *What connects us-Ce qui nous lie project* Dementia Community Investment fund (1920-HQ-000092), to support the aim to create a web of inter-sectoral resources and decrease stigma. In addition to the stratified matching, the program has been further modified for TIP-OA to address the needs of older adults during COVID-19 with feedback from trainers, clinicians, and volunteers.

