#### Client Referrals, Screening and Matching

Clients are either self-referred or referred from the JGH (COVID-19 inpatient units or the geriatric psychiatry clinic), long-term care facilities, local primary care clinics, or community organizations in the west-central Montreal healthcare/administrative catchment region (which represents over 500,000 residents from diverse ethnic backgrounds). Interested clients and clinicians can call our voicemail number, send an email, or fill out a form on our website to refer to our program. Included clients are consenting older adults (age ≥ 60) living in Montreal. Excluded individuals (1) are actively suicidal, (2) have a severe hearing impairment or other disability preventing the use of a phone, or (3) are suffering from moderate or severe dementia, as determined by clinical judgment (e.g., based on client history and/or past memory testing), or (4) are unable or unwilling to provide informed consent.

At intake, the screening clinician or trainee (e.g., in psychiatry, social work, psychology) spends 20–30 min on the phone with each client to collect basic demographic information and perform an informal clinical assessment regarding the client's level of cognitive functioning (coded as having suspected mild dementia or not). In cases where the client was referred from a clinic, our clinical team receives information from the referring clinician regarding the clients' cognitive and overall functioning. The screening clinician also assesses the client's level of risk and the complexity of their case, conducting a brief assessment developed primarily from Culo's paper (26) and national guidelines pertaining to seniors' mental health (27). This risk assessment is flexible and allows for the consideration of factors that are not included in the assessment, but that may hamper communication between the client and volunteer. The team then stratifies clients into categories based on case complexity and the initial risk assessment (Appendix B in Supplementary Material). Although we only assess case complexity at baseline, communication with volunteers through various channels (see section Volunteer Support and Quality Assurance) typically informs us of client mobility between categories. Following client screening and categorization, a clinician and volunteer manager assign clients to newly trained volunteers according to their assigned categories on a weekly basis.

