#### Client Quantitative Outcome Measures

All primary and secondary outcomes will be assessed over the phone at baseline, 4-, and 8-weeks (primary study endpoint):

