#### Client, Volunteer, and Stakeholder Qualitative Outcome Measures

*Zoom*^*TM*^
*focus groups* will be conducted at an 8-week follow-up with 16 volunteers (eight per group) and eight clinicians/stakeholders, who will be consecutively selected and invited over the phone to participate. Verbal informed consent will be obtained before the start of the focus groups.

*Semi-structured interviews:* 10 different stakeholders (e.g., referring clinicians, clinical team, coordinators, community partners), 15 volunteers, and 25 clients (consecutively selected) will additionally be invited to participate in individual semi-structured interviews, for which verbal informed consent will be obtained. The client interviews will consist of open-ended and guided questions regarding the overall program and its impact on their mental health and well-being (see Appendix C in Supplementary Material). The main purposes of the volunteer and stakeholder focus groups and interviews are to analyze their experiences (including challenges and opportunities encountered) and to assess the strengths, weaknesses, and viability of the program. For example, volunteer focus groups and interviews inquire about the types of issues encountered when dealing with clients, their ability to provide clients with support, and their experience accessing support from the TIP-OA team. Stakeholder focus groups and interviews include questions about their comprehension of the program procedures, their perception of the program's impact on clients, and their ability to work with the TIP-OA team.

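### The only stated mode for the 25 client interviews is Zoom, at odds with the protocol's reasons for using the telephone and likely to under-represent clients without internet access

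*Protocol article*

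**What the plan says.** The article describes the client interviews in two places.

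- **Client, Volunteer, and Stakeholder Qualitative Outcome Measures (Methods):** Zoom is attached to the focus groups of volunteers and clinicians/stakeholders. The interviews follow in a separate paragraph: "25 clients (consecutively selected) will additionally be invited to participate in individual semi-structured interviews". No mode is given.
- **Results—Early Experience:** "25 clients, 15 volunteers, and 10 stakeholders will be selected in the same manner for semi-structured interviews on Zoom". Here the platform applies to all three groups, clients included.

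Recruitment and Training of Volunteers describes Zoom as "a widely used video conferencing platform".

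Four other statements bear on how clients can be reached.

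- The Introduction reports that "one survey found that only 10% used the internet, while 72% owned a cell phone".
- It adds that "many telehealth interventions requiring advanced digital literacy are likely unfeasible for rapid implementation", and concludes that "telephone-based care is likely able to serve the largest proportion of older adults".
- Client Referrals, Screening and Matching excludes people who "have a severe hearing impairment or other disability preventing the use of a phone". It sets no internet or device requirement.
- Client Quantitative Outcome Measures states: "All primary and secondary outcomes will be assessed over the phone at baseline, 4-, and 8-weeks (primary study endpoint".

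Digital literacy is measured with a 14-item scale (Additional measures/covariates) but is not linked to interview selection or mode. Strengths and Limitations does not mention interview mode.

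**The concern.** The telephone was chosen because many older adults are not online, yet the one stated mode for hearing clients' own accounts is a video platform. A client can meet every entry criterion, receive every call and complete every outcome scale without internet access, and still be unable to take up the interview as described.

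The third study objective is to analyse the experiences of those involved, clients among them, and the client interviews ask about the programme's effect on mental health and well-being. Consecutive selection is meant to avoid picking informants by convenience. If the invitation can be accepted only by video, the interviewed group is filtered by internet access after selection. The Discussion says the evaluation should identify roadblocks for future telephone-based support, and clients who have only a telephone are important informants for that.

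**Working it through.** The plan gives no figure to reproduce here, so the main check compares the sections.

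**Step 1. Is the mode stated?** The Abstract lists interviews without a mode. The Methods section on qualitative outcomes gives a mode for the focus groups only. Results—Early Experience says Zoom. One of three places states a mode, it states video, and none mentions a telephone interview for clients.

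**Step 2. What access does each client contact need?**

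| Contact with clients | Mode stated | Section |
|---|---|---|
| Intake screening | Telephone | Client Referrals, Screening and Matching |
| Intervention | Telephone | Interventional Methods |
| Outcome scales | Telephone | Client Quantitative Outcome Measures |
| Interviews | Zoom | Results—Early Experience |

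Healthcare utilization comes from medical records and needs no contact. The interview is the only client contact in the table that asks for more than a phone.

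**Step 3. What would determine the size of the skew?** Let *p* be the share of clients able to join a video call. Suppose an experience is reported by a share θ₁ of those clients and θ₀ of the rest. Interviews open to all would find on average *p*θ₁ + (1 − *p*)θ₀. Video-only interviews would find θ₁. The difference is (1 − *p*)(θ₁ − θ₀). The article gives neither *p* for its own clients nor any basis for θ₁ − θ₀, so the difference cannot be computed.

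**Step 4. Illustration over a range of *p*.** The 10% is the survey figure cited in the Introduction. The values 20% to 50% are assumptions. Expected number able to join among 25 consecutive clients = 25*p*. Approaches needed on average for 25 interviews = 25/*p*. The last column is the exact binomial probability of at least 25 video-capable clients among the 200 in the quantitative sample.

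| *p* | 25*p* | 25/*p* | P(at least 25 of 200) |
|---|---|---|---|
| 10% | 2.5 | 250 | 0.14 |
| 20% | 5 | 125 | 0.998 |
| 30% | 7.5 | 83 | 1.000 |
| 50% | 12.5 | 50 | 1.000 |

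The article does not say whether interviewees come from the 200 research clients or from all clients (305 as of October 15th, 2020). With 305 and *p* = 10%, the probability of at least 25 is 0.88.

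Two things follow. From 20% upward, recruitment would not fail. But throughout this range, filling the 25 places by video alone means passing over at least half of the clients in sequence (1 − *p* of 50% or more). The issue is therefore who is interviewed, more than whether 25 can be found.

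**The case against.** The strongest reply is that Results—Early Experience is a status paragraph that compresses all the qualitative work into one sentence. The governing Methods text separates focus groups on Zoom from interviews with no platform named, so the mode may simply be open. The article also condenses a fuller protocol, its interview appendix is not shown, and arrangements for clients who cannot use video are the kind of detail left to such documents. The team already telephones its clients and could do so here.

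Much of this stands. The two sections can be read as one open and one abbreviated. It does not remove the point, because the article does state a mode for client interviews and that mode conflicts with its own reasoning. If telephone was intended, the sentence is wrong as written. If Zoom was intended, the client-experience component is at risk.

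Three stronger readings are tempting and are not supported:

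- **That the interviews exclude clients who are not online.** No section says such clients are ineligible, skipped or refused a call. Under-representation is a likely consequence of following the text, not a stated rule.
- **That about 250 clients would have to be approached.** This applies one survey's 10% to this programme's clients. The survey's population, place and date are not given in the article. Some clients are evidently expected to be online, since self-referral is possible by email or web form and consent forms may be emailed.
- **That video-capable clients are younger, less isolated or less cognitively impaired, so that the direction of bias is known.** The article gives no source for such a profile.

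The plan also triangulates across sources and measures digital literacy, so a skew could be described afterwards. That helps interpretation but does not bring in the clients who were not heard.

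**Conclusion.** The point holds as an inconsistency with a likely consequence. The only stated mode for the client interviews is video, which conflicts with the rationale for telephone delivery, the phone-only access requirement and the phone-based collection of outcome scales. If followed as written, it is likely to under-represent clients without internet access.

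The size is unknown. The conclusion assumes that the Zoom statement means what it says for clients, that some clients cannot join by video, and that no unstated telephone alternative is offered. For the themes themselves to be distorted, experiences must also differ by access, which is plausible but not shown.

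The effect is confined to the qualitative client component. The primary outcome (PSS), the other scales and healthcare utilization do not depend on it.

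**What to change.** Reconcile the qualitative outcomes section of the Methods with Results—Early Experience:

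1. State in both that client interviews are held by telephone, with Zoom if the client prefers.
2. Keep Zoom for the focus groups and for interviews with volunteers, clinicians and stakeholders.
3. Report how many client interviews were held in each mode, and describe the interviewed clients by the digital literacy score already planned under Additional measures/covariates.

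This needs a change of wording in the protocol and the interview procedure, with no new instrument and no change to the quantitative analysis. The drawback is the loss of visual cues in telephone interviews. Reporting the mode lets readers judge whether accounts given by phone and by video differ.
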